**Fig. 3 Fig3:**
[figure not shown]
Flow diagram Phase 1 of the ZAQ-study. Patients will undergo clinical evaluation and be divided into 3 groups: Patients with an ASD (Autism Spectrum Disorder) diagnosis, SD (schizotypal Disorder) diagnosis, neither ASD nor SD diagnosis. In parallel and independent from the clinical evaluation, participants will be assessed with the ZAQ schiZotypy Autism Questionnaire), RAADS-R-DK (Ritvo Adult Aspergers diagnostic Schedule – Revised – Danish translation) and SPQ (Schizotypy Personality Questionnaire)

### Considerations related to the statistical analysis

#### Statistical models and analyses

##### Factorial evaluation

First, the dimensionality of the ZAQ will be evaluated with confirmatory factor analysis (CFA). If modification indices suggest a better fit from altered subscales, e.g., by relocating individual items to other subscales, these hypotheses will be included in the subsequent unidimensional tests.

##### Unidimensional construct evaluation

Responses to the proposed subscales of the ZAQ will each be analysed with a unidimensional item response theory (IRT) model. The 1-parameter logistic Rasch model represents the gold standard of construct validation and offers stronger inferences than less restricted models. If applicable, violations of the assumption of local dependence and no differential item functioning (DIF) may be accommodated by the extended graphical log-linear Rasch model [49]. If the assumption of *tau* equivalence is violated and this cannot be solved — e.g., by excluding a minimal number of under-discrimination items — a more flexible 2-parameter logistic model may be adapted.

##### Deriving a general factor

The results of the unidimensional results will be used to select an appropriate multidimensional model in which all subscales reflect a general ZAQ trait. If no indications of DIF were found, a higher-order CFA model will be used, specified in line with the validated unidimensional model (e.g., item interaction terms and/or loading restrictions if applicable). Otherwise, a multidimensional IRT model will be used, ensuring an unbiased trait estimation across subgroups.

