## Abstract

**Background:**

Autism spectrum disorder (ASD) and schizotypal disorder (SD) both have a heterogenous presentation, with significant overlaps in symptoms and behaviour. Due to elevated recognition and knowledge of ASD worldwide, there is a growing rate of referrals from primary health professionals to specialised units. At all levels of assessment, the differential diagnostic considerations between ASD and SD exert major challenges for clinicians. Although several validated screening questionnaires exist for ASD and SD, none have differential diagnostic properties. Accordingly, in this study, we aim to develop a new screening questionnaire, the schiZotypy Autism Questionnaire (ZAQ), which provides a combined screening for both conditions, while also indicating the relative likelihood of each.

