## Background

The psychiatric burden in people with Autism Spectrum Disorder (ASD) [1] is considerably higher compared to neurotypical individuals, with 70% experiencing at least one co-occurring psychiatric disorder and 40% exhibiting two or more psychiatric disorders [2]. In a clinical setting and at all levels of assessment, one of the most difficult differential diagnostic challenges is schizotypal disorder (SD), which shares considerable features with ASD both at the symptomatic level and in the diagnostic criteria (see Fig. 1). Thus, discriminating ASD from SD in a clinical setting is a time-consuming task and demands a high level of expertise of both disorders. An audit of 319 patient cases at our clinic (specialized unit for the assessment of ASD) from January-June 2019 showed that about 37% of the adults referred to our clinic for the assessment of ASD, did not meet diagnostic criteria. Of these, almost 40% were diagnosed on the schizophrenia spectrum (predominantly SD). To improve diagnostic accuracy, it is therefore not only pertinent but also necessary to investigate discriminating features between ASD and SD and to develop tools to aid clinicians in the assessment.

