**Fig. 2 Fig2:**
[figure not shown]
Development of concepts and criteria (figure provided by [name])

ASD has its roots in the relatively young field of child and adolescent psychiatry, whereas SD comes out of a more than 100-year-old tradition and is primarily based on clinical presentations in adults. Consequently, professionals involved in assessment of ASD and SD often come from different backgrounds and make use of different diagnostic methods. The prevalence estimates of ASD display a high variability across nations worldwide. In most western countries the prevalence is estimated to be 1–2% [3]. Danish data suggest a prevalence of 1.65% or approximately 95,000 persons in Denmark [4]. The case identification and assessment of ASD is challenged by a high rate of comorbidity with depression (50%), anxiety (40%) and ADHD/ADD (40–60%) [5, 6]. The prevalence of comorbidity with SD has to our knowledge not been established. Nevertheless, some indications of the relation between ASD and SD can be estimated by looking at studies comparing ASD with psychosis or schizophrenia spectrum disorders (SSD). Sub-clinical psychotic symptoms occur frequently in ASD patients [7–9], and the prevalence of SSD in adults with ASD are in the range of 4–12% [5].

To aid in case identification of ASD, several screening questionnaires have been developed, including the Autism Spectrum Quotient (AQ) [10], the Ritvo Adult Asperger Diagnostic Scale Revised (RAADS-R) [11], and the Social Responsiveness Scale (SRS) [12]. Importantly, however, several studies indicate that such questionnaires do not differentiate well between autistic individuals and individuals with SSD [13, 14].

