## Methods

### Description of the creation of ZAQ

To construct the ZAQ, we first performed an exhaustive literature search to identify potential discriminating features between ASD and SD. Complementing the literature search, we interviewed three experienced clinicians who identified discriminating factors based on their clinical knowledge. Altogether, we identified 38 features which appeared to differentiate ASD and SD. These features constituted 11 subscales, subsumed under 6 subdomains (see Table 1). Identification of potentially discriminating features has been the primary focus. Once identified these features were grouped together into well-defined subscales. To present an overview, these subscales are grouped together in subdomains, highlighting the areas showing potential for discrimination [28, 29].

**Table 1 Tab1:** Summary of the domains, subdomain and subscales serving as the theoretical framework for ZAQ^a^

**Main ZAQ-domains**	**Subdomain**	**Subset of items on which responses between individuals with ASD or SD might differ**	**Subscales**	**Number of questions**
**Diagnostic criteria**	Autism	Stereotyped behavior, narrow interests, hyper-hyposensitivity to sensory stimuli	1. Steretyped behavior	14 questions
			2. Hypersensitivity + Narrow interest	11 questions
	Schizotypy	Self-disorders, hyper-reflexitivity, magical ideation, positive schizotypy	3. Self-disorders	17 questions
			4. Magical ideation + positive schizotypy	13 questions
			5. Disorganised schizotypy	5 questions
			6. Negative schizotypy	10 questions
**Clinical features**	Clinical trajectories	Time of onset of symptoms, childhood symptoms	7. Clinical trajectories and symptoms	19 questions
**Psychological theory**	Theory of Mind (ToM)	Inference of intentions of others, ToM performance, self-referential hypermentalisation, facial emotion perception	8. Theory of Mind	13 questions
	Local vs. global processing	Local vs. global processing, imagination and creativity, reading abilities, word interpretation, savant feature, apophenia	9. Local vs. global processing	8 questions
**Cognitive features**	Attention, memory	Selectivity of attention, selective memory/false memory, working memory performance	10. Cognition	12 questions
			11. Higher Cognitive Functions	9 questions

^a^Note: For a comprehensive account, see also references [28, 29]

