##### Concurrent validity and screening accuracy

The latent ZAQ estimate will be evaluated against the diagnostic outcome using logistic regression and a receiver operating characteristic (ROC) curve. The predictive power is evaluated by the area under the curve (AUC) and the sensitivity and specificity at their equilibrium, reflecting equal importance of correct identification in both groups. To promote the generalisability of the results, K-fold cross-validation will be used to dynamically divide the sample into training and testing subsamples.

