### Outcome

We hypothesize that the ZAQ will provide acceptable discrimination between ASD and SD, as indicated by an AUC ≥ 0.7. The ZAQ will retain a clinically meaningful factor structure, instructing further research on distinct sub-constructs. Lastly, the positive predictive value of the cut-off score will have strong clinical power regarding the selection of which patients need further diagnostic examination in either a specialised clinic for the assessment of psychotic disorders or a clinic for the assessment of ASD.

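### The planned ROC uses one general ZAQ trait built from all subscales; this may understate ASD-versus-SD discrimination, and one axis is unlikely to serve both stated aims

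*Protocol article*

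**What the plan says.** Table 1 of the protocol article lists 11 subscales: two for autism, four for schizotypy and five for other domains (clinical trajectories, Theory of Mind, local versus global processing, and two on cognition). After the unidimensional analyses, the section Deriving a general factor will "select an appropriate multidimensional model in which all subscales reflect a general ZAQ trait". Without differential item functioning this is a higher-order CFA. Otherwise "a multidimensional IRT model will be used, ensuring an unbiased trait estimation across subgroups", again with the trait in the singular.

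The accuracy step then reads: "The latent ZAQ estimate will be evaluated against the diagnostic outcome using logistic regression and a receiver operating characteristic (ROC) curve" (section Concurrent validity and screening accuracy). No separate autism and schizotypy scores, and no contrast between them, are named for this step. Accuracy is read at the point where sensitivity and specificity are equal, and the Outcome section likewise refers to one cut-off score.

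The aims are wider than one axis. The abstract describes a tool that "provides a combined screening for both conditions, while also indicating the relative likelihood of each". The Outcome section hypothesises "acceptable discrimination between ASD and SD, as indicated by an AUC" of at least 0.7.

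**The concern.** A common factor captures what its indicators share. What separates ASD from SD should lie largely in the profile: autism subscales high relative to schizotypy subscales, or the reverse. A higher-order factor with loadings of one sign leaves most of that profile in the first-order residuals, and the residuals are not taken to the ROC.

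The article's own premises point to loadings of one sign. The Background says that SD "shares considerable features with ASD both at the symptomatic level and in the diagnostic criteria", and of existing autism scales that "several studies indicate that such questionnaires do not differentiate well between autistic individuals and individuals with SSD". ZAQ items were drawn from existing autism and schizotypy instruments. The Power calculation section sizes the factor analysis on a combined clinical and non-clinical sample of 500. If the model is fitted on that sample, the 200 controls pull the factor towards case-versus-control severity.

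At stake is the main hypothesis. The planned AUC could fall short of 0.7 although the same responses hold enough information to reach it. Conversely, good separation of patients from controls could be mistaken for differential diagnostic value.

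**Working it through.** **Inputs from the article.** Groups: 200 ASD, 100 SD, 200 controls. Item counts from Table 1: autism 14 + 11 = 25; schizotypy 17 + 13 + 5 + 10 = 45; subscales 7 to 11, 19 + 13 + 8 + 12 + 9 = 61. The total is 131, whereas the text says 130; this does not affect the point. The success threshold is an AUC of 0.7.

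**The plan's own figure.** The sample-to-item ratio reproduces: 500/60 = 8.3, stated as 8:1. It concerns factor stability and says nothing about the AUC, for which no sample size is given.

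**Assumptions.** The article gives no loadings, subscale correlations or group means. All such values below are assumed.

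**Closed form, two dimensions.** Let A (autism) and S (schizotypy) have unit within-group variance and correlation 0.5. Relative to controls, each patient group is raised by 1.5 on its own dimension and 0.75 on the other. For a normal score with standardised group difference d, AUC = Φ(d/√2).

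- Equal-weight sum A + S: both groups average 2.25, so d = 0 and the ASD-versus-SD AUC is 0.50.
- Sum weighted 25:45: ASD 25×1.5 + 45×0.75 = 71.25; SD 25×0.75 + 45×1.5 = 86.25; difference 15. Variance 25² + 45² + 2×0.5×25×45 = 3775. d = 15/√3775 = 0.244, AUC = 0.569.
- Contrast A − S: difference 0.75 − (−0.75) = 1.5, variance 1 + 1 − 2×0.5 = 1, AUC = Φ(1.5/√2) = 0.856.

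For patients against controls the ranking reverses:

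- Sum: d = 2.25/√3 = 1.30, AUC = 0.82.
- Contrast: ASD lie above controls (AUC Φ(0.75/√2) = 0.702) and SD lie below (0.298). With patients mixed 2:1 the AUC is (2×0.702 + 0.298)/3 = 0.57.

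**Simulations with 11 subscales and the planned group sizes.** One common factor was extracted from the pooled 500. Its ASD-versus-SD AUC was compared with that of scores retaining the contrast.

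| Assumed situation | General trait | Contrast-retaining scores |
|---|---|---|
| Two correlated dimensions (0 to 0.5); own elevation 1.0–1.5 SD, other 0.5–1.0 SD | 0.54–0.63 | 0.69–0.83 |
| Shared severity plus an ASD–SD axis; equal severity; all loadings positive | 0.55–0.60 | 0.70–0.88 |
| As the second row, but groups differ in overall severity | 0.57–0.80 | 0.82–0.86 |
| Weak shared severity, some loadings negative (bipolar) | 0.75–0.85 | 0.80–0.82 |

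In rows two to four the comparator is a linear discriminant tested on a held-out half, and the general-trait AUC is taken in whichever direction favours it.

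**Dependence on subscales 7 to 11.** A further set of runs used own elevation 1.25 SD, other 0 to 0.75 SD and correlation 0 to 0.5.

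- Subscales 7 to 11 load on both dimensions: general trait 0.54–0.60.
- Split between the dimensions: 0.53–0.84.
- Themselves discriminating: at correlation 0 to 0.3 the trait is bipolar and loses essentially nothing (0.68–0.91 against 0.68–0.91 for two scores). At correlation 0.5 it gives 0.63–0.93 against 0.72–0.93.
- In the clearest bipolar cases the same trait separated patients from controls with an AUC of only about 0.46–0.56.

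**The case against.** A reader might infer that the general trait must miss the ASD–SD difference, because every subscale loads with the same sign. The documents do not support that. They report no loadings, and the overlap evidence concerns the disorders and older autism scales, not the selected ZAQ items. The content was chosen for the opposite property: "Altogether, we identified 38 features which appeared to differentiate ASD and SD", and clinicians then cut about 950 questions to 195. A bipolar factor is therefore possible, and in the bipolar scenarios the loss is small or absent. The 0.50 in the closed form also follows from the symmetry assumed there, and the lowest contrast-based result, 0.69, itself falls just short of the target.

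A reader might also infer that a useful questionnaire would be discarded. That too goes beyond the text. Phase 1 is not a go/no-go test. The Post-hoc analysis section tests each item against diagnosis by logistic regression, allows the model to be modified towards predictive items and carries the result to Phase 2 as a hypothesis. A random forest on the combined sample may follow. This is a real route for discriminating information, but it is labelled post hoc, and the random forest depends on how far the ZAQ changes between phases. The planned accuracy analysis remains the ROC of the general trait.

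Finally, a condensed article may leave scoring detail to a fuller plan. Here, though, the article itself states which score enters the ROC. Nor does the planned K-fold cross-validation alter what that score measures.

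**Conclusion.** The concern holds in a conditional form. The article passes one general trait to the ROC. If ASD and SD patients are both elevated on overlapping features, are similarly severe, and are modelled together with controls, that trait is expected to reflect mainly shared severity. Its ASD-versus-SD AUC is then about 0.54–0.63, against about 0.69–0.88 when the autism–schizotypy contrast is kept. These figures rest on assumed loadings and elevations. The pooled fit is inferred from the Power calculation section; the factor section does not state it.

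The loss is smaller or absent if the groups differ in severity or the factor is bipolar. The bipolar case does not rescue the design, because a score that then separates ASD from SD well separates patients from controls poorly. The article does not reconcile a single trait with a tool meant both to screen for two conditions and to give the relative likelihood of each. Confidence is moderate. The plan should be improved on this point before the Phase 1 data are analysed, but this is not a fatal flaw.

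**What to change.** In Deriving a general factor, keep the higher-order CFA or multidimensional IRT model for construct validity, and report the general trait as an overall severity score.

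In Concurrent validity and screening accuracy, enter the validated subscale scores, including subscales 7 to 11, into a cross-validated (multinomial) logistic regression. Alternatively, enter correlated autism and schizotypy trait scores; the plan must then say to which trait each of subscales 7 to 11 belongs, since they hold 61 of the 131 items counted in Table 1. Base the ASD-versus-SD AUC, its comparison with 0.7 and the relative likelihoods on the predicted probabilities from that model.

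The cost is a change of wording and a few more regression parameters than with a single predictor, so somewhat more risk of overfitting with 100 SD patients, which the cross-validation already planned can address. No new data are needed.

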##### Concurrent validity and screening accuracy

The latent ZAQ estimate will be evaluated against the diagnostic outcome using logistic regression and a receiver operating characteristic (ROC) curve. The predictive power is evaluated by the area under the curve (AUC) and the sensitivity and specificity at their equilibrium, reflecting equal importance of correct identification in both groups. To promote the generalisability of the results, K-fold cross-validation will be used to dynamically divide the sample into training and testing subsamples.

##### Post-hoc analysis

A post-hoc analysis driven by the diagnostic data can increase model performance, while also posing a risk of overfitting the model to the data and thereby reducing the generalizability of the results. To counteract the latter, only modifications considered clinically meaningful by the clinical experts of the research group will be incorporated, and results will either serve purely as hypotheses or will be stabilised with bootstrap aggregation.

In Phase 1, the diagnostic discrimination of each item is evaluated with logistic regression on the diagnostic outcome. Where clinically meaningful, the model will be modified to promote the influence of highly predictive items while also retaining parsimony. The resulting model will serve as a hypothesis in Phase 2.

For the Phase 2 post-hoc analysis, the suitable procedure will depend on the consistency of the ZAQ across Phase 1 and 2. If the ZAQ was mainly shortened, with limited modifications to the items carried over to Phase 2, it will allow for a supervised machine learning based-model on a combined Phase 1 and Phase 2 sample. This analysis will use a random forest algorithm and overfitting will be controlled by bootstrap aggregation and by splitting the sample into training and validation sets. Otherwise, the post-hoc analysis procedure of Phase 1 will be repeated, to inform hypotheses for future studies.

#### Power calculation

Acceptable diagnostic prediction by the ZAQ would manifest as an AUC ≥ 0.7 in the ROC analysis [50]. Establishing this with confidence relies on the variance of the ZAQ trait estimate, which can only be estimated at Phase 1 completion. For the factor analysis, no formal consensus exists for the minimum sample size [51]. While a minimum of *n* = 200 is a popular rule of thumb, Kline [52] suggests an ideal sample-to-item ratio of 20:1 in CFA. This corresponds to *n* ≤ 360 for the separate subscales (≤ 18 items) and 2600 at the aggregate level (130 items). Assuming the ZAQ is abbreviated to 60 items for Phase 2 and taking into account the stabilising effect of pilot testing, we may reasonably consider a combined clinical and non-clinical sample of 500 to provide a ratio of 8:1. This ensures reasonable factorial stability at the aggregate level while offering excellent statistical power at the subscale level.

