**Methods:**

We aim to test 200 autistic patients and 100 schizotypy patients recruited from specialised psychiatric clinics and 200 controls from the general population (Phase 1). The results from ZAQ will be compared to the clinical diagnoses from interdisciplinary teams at specialised psychiatric clinics. After this initial testing phase, the ZAQ will be validated in an independent sample (Phase 2).

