### Schizotypal disorder

SD is also a heterogeneous disorder with an estimated prevalence of 4.6% and a high rate of comorbidity [15, 16]. The diagnosis can be made if at least 4 out of 9 ICD-10 criteria are met (see Fig. 1). Although debated [17], SD is considered a crucial construct in the development of SSD [18]. Thus, early diagnosis is important for prognosis, as 25–48% of SD patients are prodromal and go on to develop SSD [17, 19]. The prevalence of comorbidity between ASD and SD, which is the main focus of this study, has to our knowledge not been described in any detail. However, the prevalence of ASD in individuals with SSD seems to be substantially increased relative to the general population, although estimates vary widely [20].

Several psychometrically robust questionnaires are available to assess features of and screen for SD. In adult populations these notably include the Schizotypal Personality Questionnaire Brief Revised (SPQ-BR) [21], the Oxford-Liverpool Inventory of Feelings and Experiences (O-LIFE) [22], the Multidimensional Schizotypy Scale (MSS) [23], the Cardiff Anomalous Perception Scale (CAPS) [24], and the Community Assessment of Psychic Experience (CAPE) [25]. In children, these notably include the Melbourne Assessment of Schizotypy in Kids (MASK) [26] and the Schizotypy Personality Questionnaire in Children (SPQ-C) [27], (see Table 2). To our knowledge, none of these have significant psychometric power to discriminate SD from ASD.

Given significant difficulties in discriminating between ASD and SD and the serious consequences that case misclassification can have for treatment and prognosis, we have sought to develop the schiZotypy Autism Questionnaire (ZAQ) to aid clinicians in the assessment of and discrimination between ASD and SD in adults at the case identification stage. A pilot version of this novel screening questionnaire ZAQ, containing 130 questions, has been developed at the Mental Health Centre, Capital Region of Copenhagen. This will be tested in 300 psychiatric patients and 200 healthy controls from May 2022 – April 2023, which constitutes Phase 1 of this study. Psychometric data analysis from this study will constitute the empirical foundation for the development of the final version of ZAQ. This final version, which pending statistical recommendations is expected to contain approximately 60 questions, will undergo subsequent validation in an independent sample (Phase 2).

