**CAPS** Cardiff Anomalous Perception Scale	Bell et al. 2006 [24]	**EASE (Semi Structured)** Examination of Anomalous Self-Experience	Parnas et al. 2005 [46]				
		**SQuEASE6** Short Questionnaire 6 of EASE	Møller 2018 [47]				
		**IPASE** Inventory of Psychotic-Like Anomalous Self-Experiences	Cicero et al. 2019 [48]				

In a first round of evaluation of their face-validity, these 950 questions were presented to six experienced clinicians—each with extensive (+ 5 years) clinical knowledge in either ASD or SD and who were not associated with the research group. These clinicians assessed how their patients would answer these 950 questions. Importantly, questionnaires measuring schizotypy were assessed by clinicians with ASD experience and vice versa. This evaluation retained 195 questions (version 2 ZAQ). All items of the version 2 ZAQ then underwent a second round of evaluation by 5 autistic patients and 2 schizotypy patients. Of these 195 questions, judged on the basis of their unambiguity and clarity, the final 130 questions entering Phase 1 of the study were selected. The resulting subscales ranged from 5–19 items.

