### Recruitment and testing

We have designed a multicenter, prospective, non-randomized experimental study, where adult patients will be recruited from May 2022 – April 2023. A group of 300 patients will be recruited from 2 outpatient clinics located at Mental Health Centre Copenhagen: 200 patients (see power calculation) will be recruited from the pool referred to the specialised clinic for diagnostic assessment of ASD at Mental Health Centre Copenhagen, and 100 patients will be recruited from the specialised psychosis clinic at Mental Health Centre with an SD diagnosis. Additionally, a group of 200 adults from the general population without a psychiatric diagnosis will be recruited as a control group. Inclusion and exclusion criteria are detailed in Table 3. The data will be collected on-line and managed through a secure server with full compliance with Personal Data Handling laws of Denmark.

**Table 3 Tab3:** Inclusion and exclusion criteria

**Inclusion Criteria: Patients 18–65 years (ASD and non-ASD psychiatric)**	**Exclusion Criteria: Patients (ASD and non-ASD psychiatric)**
WAIS-IV or Raven IQ > 85, no-clinical suspicion of intellectual disability and minimum 11 years of education	Insufficient Danish language skills
Completion of: - Clinical Assessment - Adult Asperger Assessment (AAA) - Psychopathology evaluation using DSM-5 - A conclusion based on multidisciplinary consensus	Acute psychiatric illness prompting departure/dismissal from the diagnostic assessment
Controls: Are matched with age, gender, marital status, number of children, and educational level	Controls: Concurrent or prior psychiatric diagnosis (self-report)

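### The 8:1 ratio supporting n = 500 uses the 60 items expected in Phase 2; the 500 participants described are the Phase 1 sample and answer 130 items, about 3.8:1

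*Protocol article*

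**What the plan says.** The protocol article assigns 500 people to Phase 1. The Background (Schizotypal disorder) says of the pilot questionnaire: "This will be tested in 300 psychiatric patients and 200 healthy controls from May 2022 – April 2023, which constitutes Phase 1 of this study". The Abstract gives the same total by group: "We aim to test 200 autistic patients and 100 schizotypy patients recruited from specialised psychiatric clinics and 200 controls from the general population (Phase 1". These people complete the long version of the instrument: "the final 130 questions entering Phase 1 of the study were selected". The shortened version of about 60 items is expected only after Phase 1 and is to be validated in a separate Phase 2 sample, whose size the article does not give.

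The Power calculation section cites a recommended ideal of 20 people per item, which gives 360 for a subscale of 18 items and 2,600 for all 130 items. It then assumes 60 items in Phase 2, credits the pilot testing with a stabilising effect, and writes "we may reasonably consider a combined clinical and non-clinical sample of 500 to provide a ratio of 8:1". Its conclusion is "This ensures reasonable factorial stability at the aggregate level while offering excellent statistical power at the subscale level".

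Recruitment and testing, which describes Phase 1, points to that section for the number of patients from the autism clinic: "200 patients (see power calculation) will be recruited from the pool referred to the specialised clinic".

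**The concern.** The numerator and the denominator of the 8:1 ratio appear to come from different phases. The 500 is the Phase 1 sample and the 60 is the Phase 2 item count, while the questionnaire that the 500 complete has 130 items.

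This matters because the models of the whole questionnaire are first fitted in Phase 1. Under Factorial evaluation, a confirmatory factor analysis of the ZAQ comes first, and modification indices may suggest moving items between subscales. Under Deriving a general factor, all subscales are joined in one general-trait model. Under Concurrent validity and screening accuracy, the latent ZAQ estimate goes into the ROC analysis. A reader who takes 8:1 as the support for these Phase 1 steps is given a figure more than twice the one that applies.

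**Working it through.** **Inputs, all from the protocol article**
- Phase 1 sample: 300 + 200 = 500 (Background, Schizotypal disorder); by group 200 + 100 + 200 = 500 (Abstract, Methods).
- Items answered in Phase 1: 130 (Description of the creation of ZAQ). The subscale counts in Table 1 add to 14 + 11 + 17 + 13 + 5 + 10 + 19 + 13 + 8 + 12 + 9 = 131.
- Items expected in Phase 2: about 60 (Background; Power calculation).
- Largest subscale: 18 items in Power calculation, 19 in Table 1.
- Phase 2 sample size: not stated.

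**Formula:** ratio = people / items; people needed = ratio × items.

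**Step 1. Reproduce the plan's figures.**
- 20 × 18 = 360 and 20 × 130 = 2,600. Both match.
- 500 / 60 = 8.33, which rounds to 8:1. This matches, but only with the Phase 2 item count as denominator.

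**Step 2. Ratio for the questionnaire that the 500 complete.**
- 500 / 130 = 3.85:1.
- 500 / 131 = 3.82:1 with the Table 1 sum.
- Relative to the stated basis: 3.85 / 8.33 = 0.46, so under half.

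**Step 3. What 8:1 would require.**
- At 130 items: 8 × 130 = 1,040 people.
- At 60 items: 8 × 60 = 480 people.
- With 500 people: 500 / 8 = 62.5, so 8:1 holds up to 62 items.

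**Step 4. Subscale level.**
- 500 / 18 = 27.8:1; 500 / 19 = 26.3:1.
- With 19 items the 20:1 figure is 20 × 19 = 380 instead of 360, still below 500. The subscale models are well supported on this yardstick.

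**Step 5. The two possible readings, side by side.**
- *500 is Phase 1.* This agrees with every other mention of 500 and with the cross-reference in Recruitment and testing. The ratio is then 3.8:1, not 8:1.
- *500 is Phase 2.* The 8:1 is then coherent, but the section gives no aggregate-level basis for Phase 1, and the cross-reference from Phase 1 recruitment leads to no such basis.

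The passage needs correcting under either reading.

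**Step 6. The cross-reference.** Recruitment and testing attributes 200 autism-clinic patients to the power calculation. The only 200 in that section is a rule-of-thumb minimum for a factor-analysis sample. No group size is derived there.

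**The case against.** The strongest reply is that the sentence is openly conditional. It says that it assumes a 60-item version in Phase 2 and counts on the effect of pilot testing, and the Background calls the 130-item instrument a pilot version. On that reading Phase 1 is the pilot and 8:1 is a fair Phase 2 ratio. The section also shows 2,600 for 130 items just before, so the gap at full length is not hidden. This reading is possible, and it is why the point concerns what the ratio refers to and not the division. It does not dispose of the problem: no Phase 2 sample of 500 is described, and Phase 1 recruitment is referred to this very section.

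A second reply is that Phase 1 data could be re-analysed on about 60 retained items, at 8.3:1. That is true, but the items would have been chosen on the same data, and the first planned factor analysis precedes that shortening.

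Several replies stand and limit the point:
- The division 500/60 is correct, so this is not an arithmetic slip.
- The 20:1 ratio is cited as an ideal, with the remark that no consensus on sample size exists. It is not adopted as a requirement, so falling short of 2,600 (500/2,600 = 19%) is not in itself a breach of the plan.
- The 8:1 ratio is not the only number offered for the sample size. The minimum of 200 and the subscale figure of 360 are also given, and 500 exceeds both.
- Much of the Phase 1 item work does not rest on the aggregate ratio. Each subscale gets its own item response model, items are also assessed one at a time by logistic regression, the general-trait model builds on the subscale results, and the post-hoc Phase 1 model is carried forward only as a hypothesis.

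**Conclusion.** The point holds as a mismatch between a relied-on figure and the data to which it is applied. For the 130-item Phase 1 analysis the ratio is about 3.8:1, not 8:1, and the stated assurance about the aggregate factor solution is not supported for the Phase 1 factor analysis and general-trait model on the document's own yardstick.

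A reader might infer more than this. One might conclude that the Phase 1 factor solution will be unstable. The document does not show that: a people-per-item ratio is a heuristic, and stability has not been assessed from loadings, communalities or model size. One might also conclude that the sample is too small or that item selection is undermined. The subscale ratio of 26:1 and the planned item-level analyses do not support that either.

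The result assumes that 500 means the Phase 1 sample, the only sample of that size described. If it means Phase 2, the defect becomes a missing aggregate-level basis for Phase 1 in the section to which Phase 1 recruitment refers. Severity: moderate.

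**What to change.** In Power calculation:
- State which phase each ratio refers to.
- Give about 3.8:1 for the 130-item Phase 1 analysis.
- Limit 8:1 to a Phase 2 sample of at least 480 people answering 60 items.
- Restrict the claim of aggregate stability to the setting where that ratio applies.
- Label the Phase 1 aggregate model provisional until Phase 2.

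In Recruitment and testing, correct or remove the pointer in "200 patients (see power calculation) will be recruited", since the power section derives no group size of 200.

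The change is one of wording. No extra participants are needed and no analysis has to be replaced. The general-trait model can stay as planned; refitting it on subscale scores would be a preference, not a necessary correction. The cost is that the stated Phase 1 ratio becomes less favourable.
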